### Sample size and statistical power

The sample size was calculated based on a power analysis conducted for the ALAS score. Effect sizes were estimated from our previous cohort study [21]. The change in ALAS scores from pre-treatment to post-treatment (8 weeks after randomization) was 7 ± 6.0 (mean ± SD) in the intervention group and 1 ± 6.0 in the waiting control group. With a power of 0.9 to detect a significant difference at P = 0.05 (two-sided), it was calculated that 28 patients would be required for each arm. Thus, allowing for a 20% dropout rate, 35 participants will need to be recruited per group.

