**Discussion:**

This is the first study to evaluate the effectiveness of a family education and support program for parents of patients with adolescent and early adulthood eating disorders based on IPT. If this type of intervention is effective, although indirect, it could be a new support method for this patient population.

*Trial registration:* Clinical Trials. gov ID NCT05840614.

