For patients with adolescent and early adulthood eating disorders, the relationship with their parents is an important interpersonal relationship. However, parents who live with individuals suffering from eating disorders often find themselves entangled in prolonged interpersonal conflicts, placing a significant psychological burden, particularly on mothers [5]. In a systematic review of the expressed emotion (EE) in eating disorders, caregivers frequently exhibit high levels of EE, particularly emotional overinvolvement (EOI) [6]. EE is an index reflecting the familial relationship and is assessed by examining the emotions expressed towards the patient by family members. High EE among caregivers is considered a natural response in situations where caregivers have little information about their patient’s treatment, feel ill-equipped to cope, and experience isolation without adequate support. Although several effective treatments for eating disorders exist [7–9], it remains challenging to provide these for everyone in need. In the context of eating disorders, high EE among caregivers has been associated with increased anxiety and depression [10], heightened caregiver distress [11], and diminished caregiving skills [11]. Although several studies suggest that parents’ EE may not consistently predict treatment outcomes, particularly in adolescents [12–14], numerous others indicate that high EE in caregivers may negatively impact outcomes of ED treatment [15–17]. In addition, many studies suggest that parents of individuals with eating disorders experience elevated levels of depression and anxiety [10, 18–20]. It has been found that highly depressed or anxious parents may struggle to effectively communicate with their children. Among mothers of individuals with eating disorders, there is a significant negative correlation between depression or anxiety and their ability to actively listen as measured by Active Listening Attitude Scale (ALAS) [21]. Moreover, parental anxiety often triggers an overprotective response that manifests as EOI. Parents’ anxiety may lead to behaviors characterized by excessive attention, over-adaptation to the situation, or attempts to conceal negative patient outcomes [10, 22].

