### Randomisation

Participants will be randomly allocated to one of the two groups in a 1:1 ratio. A computer randomization system will generate the random allocation sequences using minimization and stratify participants according to their ability to engage in active listening (ALAS score cutoff of 36 points).

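### The 28 evaluable participants per arm stated for 90% power do not follow from the stated inputs, which need 22 or 23 per arm; 28 gives about 96% power

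*Protocol article*

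**What the plan says.** All of the planning figures are in the Sample size and statistical power section of the protocol article.

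- Effect: change in the ALAS from before treatment to 8 weeks of "7 ± 6.0 (mean ± SD) in the intervention group and 1 ± 6.0 in the waiting control group".
- Power and test level: "With a power of 0.9" "to detect a significant difference at P = 0.05 (two-sided").
- Result: "it was calculated that 28 patients would be required for each arm".
- Dropout: a 20% allowance takes this to 35 per group, which agrees with the 70 in the Abstract.

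The Randomisation section adds the allocation: "Participants will be randomly allocated to one of the two groups in a 1:1 ratio". The Data analysis plan names analysis of covariance at 8 weeks, or a maximum likelihood mixed model if data are missing. No allowance for clustering, multiplicity or a non-parametric test is stated. The section attributes the effect sizes to the research group's previous cohort study.

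**The concern.** The section gives every input of a two-group comparison of means and then a result, so a reader can repeat the calculation. The stated difference equals the stated SD, and an effect that large needs clearly fewer than 28 per arm at 90% power.

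This is the only sample-size justification in the article, and it supports the primary endpoint. If the inputs and the result disagree, at least one printed figure is wrong. What that means depends on which one:

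- If 28 is wrong, the trial has more power than it claims.
- If the difference or the SD is wrong, the article misstates the effect or the variability it was planned on, and the apparent reserve of power is not there.

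**Working it through.** **Inputs.** Difference δ = 7 − 1 = 6; SD σ = 6.0 in both arms; two-sided α = 0.05; power 0.90 (all from Sample size and statistical power); 1:1 allocation (Randomisation). Standardised effect d = 6/6.0 = 1.0.

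**1. The plan's own figure.** Normal approximation, per arm:

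n = 2(z₀.₉₇₅ + z₀.₉₀)²/d² = 2(1.960 + 1.2816)²/1² = 21.01, rounded up to 22.

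Two-sample t-test (noncentral t): n = 22.02, rounded up to 23. Power is 0.8997 at 22 per arm and 0.912 at 23. The stated 28 is not reproduced.

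**2. Power at 28 evaluable per arm.**

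- Normal: Φ(√(28/2) × 1.0 − 1.960) = Φ(3.742 − 1.960) = Φ(1.782) = 0.963.
- t-test: 0.957.

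**3. Dropout step.** 28/0.8 = 35, and 2 × 35 = 70, so the inflation itself is correct. Starting from the stated inputs, 23/0.8 = 28.75, rounded up to 29 per arm (58 in total). With 22 it is 22/0.8 = 27.5, rounded up to 28 per arm (56 in total).

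**4. Could another method give 28 from the same difference and SD?**

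| Variant | n per arm |
|---|---|
| One-sided 0.05, power 0.90 | 18 |
| Two-sided 0.025, power 0.90 | 25 (normal), 27 (t) |
| Two-sided 0.01, power 0.90 | 30 (normal), 32 (t) |
| Two-sided 0.05, power 0.80 | 16 (normal), 17 (t) |
| Two-sided 0.05, power 0.95 | 26 (normal), 27 (t) |
| Mann-Whitney inflation, usual to worst case | 23 to 26 |
| Baseline adjustment, assumed correlation of change with baseline 0.3 | 21.01 × (1 − 0.09) = 19.1, so 20 |
| Baseline adjustment, assumed correlation 0.5 | 21.01 × (1 − 0.25) = 15.8, so 16 |

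None gives 28. The planned analysis of covariance would lower the number, not raise it.

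**5. Which changed input would give 28?** At two-sided 0.05 and power 0.90, 28 per arm detects d = 0.882 by the t-test. That is 0.882 × 6.0 = 5.3 points at SD 6.0, or a 6-point difference at SD 6/0.882 = 6.8.

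**The case against.** The strongest reply is that nothing is lost. On the stated inputs the trial is larger than it needs to be, the article calls it a pilot, the intended effect is printed, and 35 and 70 follow correctly from 28. This limits the consequence and means enrolment need not change. It does not make the stated result follow from the inputs.

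A second reply is that 23 is not the one correct answer: it belongs to an unadjusted t-test on change and presumes that the inputs are right and the 28 is wrong. That also stands. The article does not show which figure is misreported, so the correction has to leave both routes open.

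Three stronger readings are tempting and are not supported.

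- **Dropout applied twice.** 22/0.8 = 27.5, rounded to 28, and 28/0.8 = 35 fits. It works only from 22. From 23 the chain is 28.75, rounded to 29, then 29/0.8 = 36.25, rounded to 37. It is a guess about how 28 arose, and the mismatch does not depend on it.
- **The source of the inputs is contradictory.** A reader might infer this because the section says "Effect sizes were estimated from our previous cohort study [21"], because the Background cites the same reference for a finding that "there is a significant negative correlation between depression or anxiety and their ability to actively listen", and because the Abstract says "This is the first study to evaluate the effectiveness of a family education and support program for parents". But that last sentence goes on to limit the claim to programmes based on IPT. One cohort study can report both a correlation and changes in two groups, and the mention of randomization may only identify this trial's time point. The cited study is not at hand, so no contradiction is shown. At most the wording is unclear on whether the values were observed or assumed.
- **The surplus is an allowance for clustering in therapy groups.** The article gives no such reason, and adding one now would be post hoc.

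**Conclusion.** The point holds as an arithmetic error in the stated sample size. Inputs of 7 against 1 with SD 6.0, two-sided 0.05 and power 0.90 need 22 (normal) or 23 (t-test) evaluable per arm, not 28. With 28 per arm, power is about 96% (0.957 by t-test, 0.963 by normal approximation).

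The direction is conservative provided that the printed inputs are the intended ones. The article does not support a reading that the trial is underpowered or that 70 is too few. Equally, the surplus power cannot be relied on until the inputs are confirmed: an SD of about 6.8, or a difference of about 5.3 points, would make 28 right at 90% power and the printed SD or difference wrong.

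These figures assume an unadjusted two-sample comparison of change scores with equal SDs and independent participants. The fault lies in a reported planning figure; it does not affect the planned analysis.

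**What to change.** Reconcile the inputs with the 28 by one of two routes.

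1. If an input (difference, SD or power) was misreported, correct it and keep 28.
2. If the inputs are right, state that they need 23 evaluable per arm, or 29 after a 20% dropout allowance. Then state that the planned 28 evaluable per arm gives about 96% power for a 6-point difference, or 90% power for 5.3 points, at SD 6.0, on an unadjusted t-test.

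In either case, add a clause saying whether 7, 1 and 6.0 were observed in the cited cohort study or are planning assumptions. Do not add a new rationale for the surplus.

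The cost is wording in one paragraph. Enrolment stays at 70, and the design and analysis do not change.

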### Data analysis plan

Statistical analysis will be performed using IBM SPSS Statistics v.26 for Windows (IBM Corp., Armonk, NY, USA). The initial descriptive statistics will summarize participant characteristics as means, standard deviations, minima, maxima, frequencies, and percentages. All analyses will be based on the intent-to-treat model. We will use analysis of covariance at 8 weeks if there is no missing data at that time. If missing data is observed, we will use the maximum likelihood mixed model, which accounts for missing data, provided that the data are missing at random, conditional on the covariates and the baseline values of the outcome. *P* < 0.05 will be set to test the null hypothesis.

## Discussion

This paper describes the study protocol for an RCT designed to investigate the effectiveness of a remote family education and support program using IPT for parents of patients with adolescent and early adulthood eating disorders. The primary outcome of this study is the active listening ability of parents at 8 weeks after randomization, and secondary outcomes include eating disorder symptoms of patients observed by parents, loneliness, social support, mental health status, and family functioning.

In patients with eating disorders, interpersonal problems are common. In particular, adolescent and early adulthood patients and their parents have difficulty in domestic communication and adjusting to the role transition, because adolescent patients undergo large and rapid changes due to physical and mental growth. The IPT concept (including interpersonal role dispute with different expectations and role transition) is expected to fit well the adolescent and early adulthood patients with an eating disorder and their parents.

The current study has several strengths. First, it is the first attempt to use IPT theory for a parental education and support program for eating disorders. Second, we created a program focusing on the role transition through changes in adolescence and early adulthood. Third, this program is a remote participation program; therefore, participants can join from anywhere in Japan. In Japan, the treatment system for eating disorders is inadequate, and with only five treatment base hospitals in the country. Many patients do not receive adequate treatment because hospitals with specialists in the treatment of eating disorders are far away. Therefore, their parents are also living with anxiety and loneliness. Fourth, we will assess not only the parents’ status but also the eating disorder symptoms of patients, as measured by the ABOS. The ABOS is a useful instrument for eating disorders with high sensitivity and specificity [48]. This trial also has limitations. Patients themselves cannot participate in this program in the current study. Naturally, treatment is best conducted with both patients and their parents according to the FB-IPT, particularly in the treatment of adolescents. Further studies will be designed for both patients and parents to participate in the program.

## Data Availability

The datasets used and/or analyzed in the current study are available from the corresponding author upon reasonable request.

## Abbreviations

ABOS: Anorectic Behavior Observation Scale
ALAS: Active Listening Attitude Scale
EE: Expressed emotion
EOI: Emotional overinvolvement
FAD: Family Assessment Device
FB-IPT: Family-based interpersonal psychotherapy
IPT: Interpersonal psychotherapy
K6: Kessler Psychological Distress Scale
RCT: Randomized controlled trial
SPS-10: Social Provision Scale 10 item
ULS: University of California, Los Angeles Loneliness Scale
